## Abstract

**Background:**

Coronary Heart Disease and Cerebrovascular Disease share many predisposing, modifiable risk factors (hypertension, abnormal blood lipids and lipoproteins, cigarette smoking, physical inactivity, obesity and diabetes mellitus). Lifestyle interventions and pharmacological therapy are recognised as the cornerstones of secondary prevention. Cochrane review has proven the benefits of programmes incorporating exercise and lifestyle counselling in the cardiac disease population. A Cochrane review highlighted as priority, the need to establish feasibility and efficacy of exercise based interventions for Cerebrovascular Disease.

**Methods:**

A single blind randomised controlled trial is proposed to examine a primary care cardiac rehabilitation programme for adults post transient ischemic attack (TIA) and stroke in effecting a positive change in the primary outcome measures of cardiac risk scores derived from Blood Pressure, lipid profile, smoking and diabetic status and lifestyle factors of habitual smoking, exercise and healthy eating participation. Secondary outcomes of interest include health related quality of life as measured by the Hospital Anxiety and Depression Scale, the Stroke Specific Quality of Life scale and WONCA COOP Functional Health Status charts and cardiovascular fitness as measured by a sub-maximal fitness test.

A total of 144 patients, over 18 years of age with confirmed diagnosis of ischaemic stroke or TIA, will be recruited from Dublin community stroke services and two tertiary T.I.A clinics. Exclusion criteria will include oxygen dependence, unstable cardiac conditions, uncontrolled diabetes, major medical conditions, claudication, febrile illness, pregnancy or cognitive impairment. Participants will be block-statified, randomly allocated to one of two groups using a pre-prepared computer generated randomisation schedule. Both groups will receive a two hour education class on risk reduction post stroke. The intervention group will receive a 10 week programme of supervised aerobic exercises (twice weekly) and individually tailored brief intervention lifestyle counselling. Both groups will be tested on week one and week ten of the programme. Follow-up at 1 year will assess longer term benefits. Analysis will test for significant changes in the key variables indicated.

**Discussion:**

Application of the Cardiac Rehabilitation paradigm to patients with ischaemic stroke or TIA has not been explored despite the obvious overlap in aetiology. It is hoped the anticipated improvement in vascular risk factors and fitness resulting from such a programme will enhance health and social gain in this population.

**Trial Registration:**

Current Controlled Trials ISCTRN90272638.

## Background

Stroke is the third leading cause of death and disability worldwide. It constitutes a formidable burden of disability for patients, their families, health professionals and the wider community. It combines aspects of both acute and chronic disease, and there is increasing evidence that those affected by stroke can benefit to a very significant extent from organised stroke care throughout the course of the illness. Delivering this care requires a combination of skills that draw on neurosciences, cardiovascular medicine, general medicine, the science of ageing, rehabilitation, vascular surgery, and public health[1].

Both coronary heart disease (CHD) and ischaemic stroke share links to many of the same predisposing, potentially modifiable risk factors (hypertension, abnormal blood lipids and lipoproteins, cigarette smoking, physical inactivity, obesity and diabetes mellitus). This highlights the prominent role lifestyle plays in the origin of cardiovascular disease [2]. Modification of multiple risk factors through a combination of lifestyle interventions and appropriate pharmacological therapy is now recognised as the cornerstone of initiatives aimed at prevention of recurrent stroke and acute cardiac events in stroke survivors [3-5].

Falling CHD and stroke mortality rates means a higher prevalence of those at risk of further events thus increasing the need for disease management, secondary prevention and cardiac rehabilitation [6]. Patients with a recent ischaemic stroke or transient ischemic attack (TIA) are at high risk for further vascular events and vascular death [7,8]. At least 15% of stroke survivors will have a second stroke during the next five years, quarter of which prove fatal within four weeks [9]. Prospective studies following TIA found incidence of stroke to be 11% within 90 days. Longer term studies found that while the risk of major vascular events- stroke, myocardial infarct (MI) and vascular death is mainly concentrated in the weeks following TIA, it remains elevated for many years afterwards [10,11].

Current evidence for secondary prevention is dominated by pharmacological interventions, while the evidence available for life-style modifications such as dietary change and physical exercise is less robust. Modification of major cardiovascular risk factors (blood cholesterol, high blood pressure and smoking) is reported to be cost-effective but needs to be better targeted if potential health gain is to be realised [12].

Given the proven benefits of regular physical activity on cardiovascular disease risk factors in able-bodied individuals [13,14] and in the post MI and coronary grafting (CABG) populations [15,16], the support for cardiovascular training in stroke survivors is growing. The need for research into the effects of such programmes has recently been highlighted as a priority by the American Stroke Association (ASA) [2] and Cochrane Review [17].

While it is reported that cardiac disease occurs in up to 75% of stroke survivors, exertion at the levels used in rehabilitation programmes after stroke is associated with low risk of serious cardiovascular complications [2]. The proposed research, which also aims to exercise this population at light to moderate i.e. submaximal intensities of ≤ 60% of their maximal heart rate, poses very low risk to the participants of adverse events and is within the recommended guidelines of the ASA at 50–80%. This is further supported by a study reporting a low frequency of medical complications during inpatient rehabilitation post stroke (No myocardial infarctions) [18]. In a scientific statement on physical activity after stroke the American Heart Association (AHA) espouse the use of aerobic conditioning post stroke to improve cardiovascular risk factors and recommend its use for stroke survivors as part of a comprehensive stroke and cardiovascular risk reduction programme [2].

The concept of cardiovascular fitness for stroke survivors has been addressed in a number of studies to date. The Cochrane review on Physical Fitness Training in Stroke Patients [17] includes 11 clinical trials. Of these however only two [19,20] included measures of aerobic fitness (VO2) and maximal work rate (Watts) as defined outcome variables. Similarly only 2 studies [19,21] described the intensity and progression of fitness training as a percentage of the participants maximal capacity, thus meeting the American College of Sports Medicine (ACSM) guidelines for developing cardiorespiratory fitness [22]. The randomised controlled trial by Potempa et al. [19] found that stroke patients could increase their cardiovascular fitness by a magnitude similar to that of healthy older adults who engage in endurance training. However, as only 7% of patients discharged from rehabilitation post stroke meet the criteria for community walking (e.g. a speed that would allow them to cross a road safely), few stroke patients are able to avail of cardiovascular training through the traditional method of treadmill training used in this study.

A cycle ergometer with adaptive devices as necessary can allow aerobic fitness training in this population of more dependent stroke survivors. Treadmill, bicycle, upper limb ergometry and step training can be used in the TIA and less disabled stroke subjects. Traditionally cycle ergometry studies have looked at exercise capacity and self concept in stroke patients following exercise training only. A study addressing exercise in men with Coronary Artery Disease (CAD) and physical disability [23] demonstrated significant increases in peak left ventricular ejection fraction and high-density lipoprotein cholesterol and decreases in resting heart rate following training.

More recent studies in the stroke population have demonstrated water based exercise [24], treadmill training [25] and a community-based exercise and mobility programme [26] can increase cardiovascular fitness after stroke, but a search of the literature has found no studies exploring the effects of an intensive programme consisting of progressive cardiorespiratory training which conforms to ACSM guidelines, accompanied by lifestyle counselling and targeted smoking cessation. These interventions are common components of 'Comprehensive Cardiac Rehabilitation Programmes' but this paradigm has not been applied to the Stroke and TIA population

### Background work

A pilot study was conducted in 2005 looking at the feasibility of a 10 week cardiovascular training programme in the non-acute ischaemic stroke population [27]. This work highlighted the efficacy of the programme in reducing cardiac risk scores and improving cardiovascular fitness in the stroke population. It also demonstrated the safety of the programme with no adverse events occurring during the exercise regime.

Focus groups were subsequently conducted with 4 groups of community dwelling stroke patients (5–6 participants per group) to establish perceived barriers to healthy lifestyle participation, preferred options for receiving information and advice and to gain end-user input into the final programme development for this clinical trial. Conversations were transcribed verbatim and subjected to thematic coding and analysis as guided by Miles and Huberman [28].

### Reason for expansion of the study

Given the proven safety record and notable benefits, it was decided to expand the study to include the post TIA population. As this population have no acquired physical disability, secondary prevention will have greater cost benefit to the health service by reducing the shared risk factors for the occurrence of stroke (currently estimated at 15% within 5 years) and development of other cardiovascular disease (CVD).

Cochrane Reviews of dietary advice, smoking cessation and stress management counselling as part of a comprehensive cardiac rehabilitation programme (CCR) in the CVD population concluded that:

• Dietary advice appears to be effective in bringing about modest beneficial changes in diet and cardiovascular risk factors over approximately 9 months but longer term effects are not known [29].

• Behavioural counselling for smoking cessation indicated that individual counselling was more effective than control. The odds ratio for successful smoking cessation was 1.56 (95% confidence interval 1.32 to 1.84). A greater effect was not detected by intensive counselling compared to brief counselling (odds ratio 0.98, 95% confidence interval 0.61 to 1.56) [30].

• Quitting smoking is associated with a substantial reduction in risk of all-cause mortality among patients with CHD. The pooled crude RR was 0.64 (95% CI 0.58 to 0.71). This 36% risk reduction appears substantial compared with other secondary preventive therapies such as cholesterol lowering which have received greater attention in recent years [31].

• Overall psychological interventions showed no evidence of effect on total or cardiac mortality, but did show small reductions in anxiety and depression in patients with CHD. Similar results were seen for stress management interventions when considered separately [32].

Although brief clinician interventions addressing physical activity and diet have been less studied than smoking cessation programmes, evidence exists that these types of interventions can influence patients to consider and adopt changes in how they eat and their physical activity levels [33,34]. Success of programmes to increase walking and other types of physical activity [34], change dietary behaviour, such as encouraging people to eat more fruit and vegetables in the 5-a-day program [36] further support clinicians' efforts to intervene in these areas.

Based on the evidence of effect of these interventions as part of CCR, adoption of the paradigm to the Stroke and TIA population appears to be warranted.

The aims of the proposed study are to determine whether a 10 week comprehensive cardiac rehabilitation programme for adults post TIA and ischaemic stroke including aerobic training, dietary and exercise advice, life skills and smoking cessation counselling:

(i) Reduces overall cardiac risk score, calculated from Blood Pressure, lipid profile, age, sex and diabetic status [38].

(ii) Increases participants' adherence to the Fourth Joint European Societies' Task Force on Cardiovascular Disease Prevention in Clinical Practice for a high risk group [39] eg by effecting a change in smoking habit as demonstrated by % reduction in smoking, healthy heart diet compliance by daily fruit(2) and veg (3)intake, habitual exercise habit, i.e. % taking moderate and/or vigorous exercise 3 times per week extrapolated from the International Physical Activity Questionnaire (IPAQ) [40].

Secondary outcomes of interest associated with the programme include: (i) Cardiovascular fitness as calculated by a submaximal cycle ergometry test of VO2 max and peak rate pressure product (PRPP). (ii) Health Related Quality of Life as measured by the Hospital Anxiety and Depression Scale scores [41], Stroke Specific Quality of Life Index [42] and Functional Health Status Charts COOP/WONCA [43].

## Methods

The Cochrane criteria for assessing methodological quality of clinical trials and the Consort checklist for publication were consulted to ensure methodological rigor in the design of this study.

### Randomisation procedure

Since blinding to the cardiac rehabilitation programme intervention is not possible, a randomised, controlled, single-blind trial is proposed. Patients recruited for this trial will be randomly assigned to a cardiac rehabilitation group and a non-cardiac rehabilitation group. Participants will be stratified into Stroke and TIA groups and block randomisation using blocks of 12 will be performed using a computer generated randomisation schedule (SPSS v12.0) prepared by an independent party in advance. Concealed allocation will be ensured through the use of opaque sealed envelopes.

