### Participant Recruitment

Subjects with ischaemic stroke will be recruited from the outpatient Stroke Rehabilitation Unit, Baggot Street Community Hospital, from the 4 community based stroke support groups. TIA subjects will be recruited from a TIA clinic in a tertiary hospital in the greater Dublin. Information leaflets will be distributed to potential subjects fulfilling the inclusion criteria in the Stroke Rehabilitation Unit database, Baggot Street Community Hospital and TIA clinic in AMNCH Hospital, with the consent of the Consultant Neurologist in this centre. Interested subjects will then contact the principle researcher (OL) should they wish to participate. Talks will be given at each support group branch meeting and information leaflets distributed. Participants will then be screened by phone to ensure they fulfil the inclusion criteria and that none of the exclusion criteria apply. The American College of Sports Medicine PARQ [22] questionnaire will be incorporated in the screening process to exclude subjects unsuitable for exercise testing. The General Practitioners of those attending the support groups will be contacted to give permission for patients to attend the programme and to consent to access medical records where necessary. A one week period between the information dissemination and consent will be given to allow due time for participants to consider the study.

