### Exclusion Criteria

O2 dependence, angina, unstable cardiac conditions, unstable diabetes, major medical conditions, claudication, febrile illness, pregnancy or cognitive impairment.

**Sample size calculations **based on the ability to detect significant differences in the key outcome variables with 80% power and p < 0.05 are indicated in table 1. Cardiac risk data was taken from the pilot study and adherence to European guidelines for lifestyle participation in a high risk CVD group was taken from baseline data of the first 50 subjects recruited to the CRAFTS trial. The formulae for detecting change in % was n > = K [P_1_(1 - P_1_) + P_2 _(1-P_2_)]/Δ^2^. The formula for detecting a change in means was n >= 2Kσ^2^/Δ^2^K = 7.8. Our pilot study [27] resulted in a withdrawal rate of 5% overall. Based on primary outcome measures of adherence to all three European lifestyle guidelines and cardiac risk score reduction with an anticipated drop-out rate of 10%, 144 participants will be recruited. 72 randomised to the intervention group and 72 to the control group.

**Table 1 T1:** Sample size calculations

	**% adherence to European Guidelines on CVD prevention in high risk group(CRAFTS baseline data)**		**Target change to detect %**	**Sample size per group**
Moderate or vigorous exercise for 20 mins 3 or more times/week	17		Increase by 20%	73
Dietary intake of 3 vegetables portions & 2 fruit portions or more/day	21		Increase by 20%	80
No smoking % in stroke and TIA patient population	85		Increase by 15%	61
% subjects fulfilling all 3 criterion	9		Increase by 20%	56
	**Mean (sd) of baseline measures from pilot study in stroke patients**	**Mean change in intervention group – pilot study**	**Target change to detect**	
Cardiac Risk Score	9.4 (6.80)	1.52	4.0	72
VO2 exercise test	10.87 (1.71)	1.48	1.0	46
HAD – Anxiety subscale	6.13 (3.71)	0.86	1.5	54

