### (a) Treatment group

The Intensive Rehabilitation Programme will consist of a 10 week schedule. Baseline measures will be taken during week 1, and an individually tailored exercise training programme prescribed. Training intensity will conform to the recommendations of the American Heart Association, American Stroke Association and American College of Sports Medicine guidelines for aerobic training in patients with cardiac risk [22]. During the subsequent 8 weeks the participants will attend twice weekly for one hour individually tailored fitness training (warm up, cycle ergometry (Motomed or Tunturi cycle ergometer) using either the upper or lower limbs, treadmill training, step work at up to 60% of their maximal heart rate). They will also attend the two hour risk reduction lecture and receive smoking cessation, physical activity and diet counselling appropriate to their needs, in accordance with the World Health Organisation (WHO) guidelines [44]. Reassessment will take place on the 10^th ^week.

The exercise sessions will be supervised by a physiotherapist (OL). Exercise will be stopped if any of the following adverse events occur: chest pain, dizziness, malaise, heart rate in excess of 60% maximal heart rate, oxygen saturation levels lower than 90% and request from participant to stop in accordance with American Heart Association guidelines for exercise testing [45]. Staff with cardiac resuscitation and defibrillation training will be on site during the exercise sessions and the cardiac arrest procedures of the community hospital will apply, immediate first aid and emergency services will be called should an adverse cardiac event occur.

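### A fixed, published block size of 12 weakens allocation concealment, because the unblinded person who delivers the programme is also the recruitment contact

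*Protocol article*

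**What the plan says.** The Randomisation procedure section of the protocol article fixes four things:

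- Strata: "Participants will be stratified into Stroke and TIA groups".
- Method: "block randomisation using blocks of 12 will be performed using a computer generated randomisation schedule", the schedule being "prepared by an independent party in advance".
- Concealment: "Concealed allocation will be ensured through the use of opaque sealed envelopes".
- Blinding: the programme itself cannot be blinded. Observer blinding then covers the outcome assessor, who is a different person.

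On who does what, Participant Recruitment has interested subjects contact the principal researcher. It continues in the passive: "Participants will then be screened by phone to ensure they fulfil the inclusion criteria and that none of the exclusion criteria apply". No role is named for that step. Under (a) Treatment group, "The exercise sessions will be supervised by a physiotherapist", and the initials there are those of the principal researcher. The Intervention section gives the same initials for the individual counselling, and for a share of the lecture that both arms attend.

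The sample size paragraph gives the totals: "144 participants will be recruited", with "72 randomised to the intervention group and 72 to the control group".

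**The concern.** The recruitment contact treats every intervention participant and so learns past allocations as the trial proceeds. That person can also see each candidate's stratum and can read the block size in the published protocol. Once six of one arm have come out of a block of 12, every remaining place in the block is determined, however well the envelopes are sealed.

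The risk is selection at entry. Several eligibility terms leave room for judgement (medical stability, major medical conditions, unstable cardiac conditions). Even a first contact can affect whether and when someone proceeds. The lifestyle outcomes (smoking, diet, exercise) are self-reported and plausibly depend on motivation, which a recruiter may sense. If more motivated people were steered to the programme, the comparison would be biased, and a blinded assessor could not undo that.

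**Working it through.** The plan states no figure for predictability, so there is nothing to reproduce first.

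**Inputs.** From the Randomisation procedure section: block size 12 and two strata. From the sample size paragraph: 144 participants, 72 per arm, which is 144/12 = 12 full blocks.

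**Assumptions.** Blocks are 6:6 (inferred from 72:72) and all are filled. Allocation is one at a time within a stratum. The observer knows the block size and every earlier allocation in that stratum.

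**Allocations known with certainty.** In a block of 2b, the last k places are all determined with probability 2·C(2b−k, b)/C(2b, b). With b = 6 and C(12,6) = 924:

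| Last k places determined | Calculation | Probability |
|---|---|---|
| 1 | 2 × 462/924 | 100% |
| 2 | 2 × 210/924 | 45.5% |
| 3 | 2 × 84/924 | 18.2% |
| 4 | 2 × 28/924 | 6.1% |
| 5 | 2 × 7/924 | 1.5% |
| 6 | 2 × 1/924 | 0.2% |

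The sum is the expected number per block: 2b/(b+1) = 12/7 = 1.71, or 14.3%. Over 12 blocks this is 12 × 1.714 = 20.6, about 21 of 144. No place before the seventh is ever certain.

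**Best-guess accuracy.** Always guessing the arm with more places left is right b + 2^(2b−1)/C(2b, b) − 1/2 times per block. For b = 6 this is 6 + 2048/924 − 0.5 = 7.72 of 12, or 64.3%. Over 144 it is about 93 correct guesses, against 72 by chance.

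**Which change helps.** The same two formulas for fixed, known sizes give:

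| Fixed block size | Certain | Best guess |
|---|---|---|
| 4 | 33.3% | 70.8% |
| 6 | 25.0% | 68.3% |
| 8 | 20.0% | 66.6% |
| 12 (as planned) | 14.3% | 64.3% |
| 16 | 2/18 = 11.1% | 10.05/16 = 62.8% |

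The entry for 16 uses 8 + 32768/12870 − 0.5 = 10.05.

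Guessing the under-filled arm needs only the running imbalance, which returns to zero after every balanced block whatever its size. Hiding the size therefore does not remove the guessing advantage, and the accuracy for a mix is the average weighted by block length:

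- Equal mix of 4, 6 and 8: (2.833 + 4.100 + 5.329)/18 = 68.1%, worse than now.
- Equal mix of 8, 12 and 16: (5.329 + 7.716 + 10.046)/36 = 64.1%, about the same as now.

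What varying sizes do remove is most of the certainty. In a simulation of the 8, 12 and 16 mix, with 72 participants assumed in each of two strata and an observer who knows the three sizes but not their order, certain allocations fall from about 14% to under 2%.

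**The case against.** A reader might infer that the physiotherapist decides eligibility and that concealment fails outright. The article supports neither. It names no one for the phone screening, so that attribution is only plausible. An independently prepared schedule with opaque sealed envelopes is a recognised safeguard, and nothing shows that it was defeated. On the figures above, about 86% of allocations are never certain, and 12 is already less predictable than fixed blocks of 4, 6 or 8.

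Other points on that side also carry weight:

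- Entry is partly controlled by others. Subjects make the first contact themselves. A standard questionnaire is built into screening, GP permission or specialist referral applies, and there is a further medical screen before exercise testing. These narrow discretion without removing it.
- The 14% is an upper bound. If a whole block were enrolled before its envelopes were opened, no inference would arise. The sample size paragraph uses baseline data from the first 50 recruits, which shows staggered recruitment but does not settle how allocation is done. Attending the shared lecture does not by itself reveal a participant's arm.
- The blinded assessor takes the baseline measures, so steering on fitness or risk score could show as baseline imbalance. Steering on motivation would not.
- Who holds and opens the envelopes is operational detail that an article may leave to the full protocol. Its absence is no defect.

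What remains is a choice the article does state: one fixed, published block size, with the unblinded deliverer as recruitment contact. The envelopes do not address inference from past allocations.

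**Conclusion.** The point holds in limited form: concealment is weakened late in each block, and the claim that envelopes ensure it is too strong. Up to 1.71 allocations per block (14%, about 21 of 144) can be known with certainty. Beyond that there is a modest guessing advantage of 64% against 50%. Both figures rest on full 6:6 blocks, one-at-a-time allocation and full knowledge of earlier allocations, so they are ceilings. They measure opportunity and are not an estimate of bias. Severity is minor to moderate: a separate assessor is blinded and others share control of entry, but selection at entry cannot be repaired afterwards.

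**What to change.** In the Randomisation procedure section, for the allocations still to be made, replace the single block size with randomly varying sizes within each stratum. The independent party already named should generate them and not disclose them to the recruiting physiotherapist. The sizes should be centred on the present one, for example 8, 12 and 16. Smaller sizes such as 4, 6 and 8 should be avoided, because they raise guess accuracy to about 68%. The text should say only that sizes vary and are withheld, and should describe envelopes as protecting concealment, not ensuring it. The new sequence should start when the current block in each stratum is complete.

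Benefit: certain allocations fall from about 14% to under 2%, and best-guess accuracy stays at about 64%. If only the first 50 have been allocated, the change reaches the remaining 144 − 50 = 94, among whom about 94/7 = 13 allocations would otherwise be certain.

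Cost: a changed setting in the schedule and one protocol sentence, with no extra patients or staff. If recruitment stops mid-block, the largest possible difference between arms within a stratum rises from 6 (half of 12) to 8 (half of 16).
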